#### Sample size

As this is a feasibility study focused predominantly on the research process [13, 14], a formal sample size calculation was not conducted. To assess whether the study’s procedures are practical and to estimate parameters like recruitment rate, treatment adherence, and variability of outcomes, a sample size of 12 per group was selected [15].

#### Recruitment

At this institution, it is estimated that approximately 50–60 pediatric patients undergo elective colorectal surgery each year. Based on a conservative recruitment rate of 60% (i.e., 2–3 patients per month), this trial will take approximately 2 years to complete.

Patients who meet the eligibility criteria will be identified by the treating staff surgeon through the Pediatric General Surgery outpatient clinic. Recruitment will begin once ethics approval is received from the Hamilton Integrated Research Ethics Board (HiREB) and Health Canada.

#### Consent or assent

The Research Coordinator will be responsible for obtaining informed consent/assent from each patient. The consent conversation will occur only after a clinical staff member within the patient’s circle of care obtains permission for the Research Coordinator to approach. Each family will receive a Letter of Information that summarizes the trial, their involvement, and potential risks. The Research Coordinator will review all this information with them, in detail as per the Tri-Council Policy Statement (TCPS-2) guidelines. The patient and/or family will also be given an opportunity to ask questions. Once informed consent is obtained, the patient will be enrolled in the study, and data collection will begin.

#### Randomization and sequence generation

Patients will be randomized to treatment groups using a computer-generated randomization list. This will consist of random blocks of multiple sizes (3, 6, 9), created by a senior biostatistician. Patients will be randomized according to a 1:1:1 parallel allocation, with an equal chance of being allocated to OA, OA + MBP, or standard care alone.

#### Concealment mechanism

The randomization scheme will be stored in Research Electronic Data Capture (REDCap), an online database housed at McMaster University [16, 17]. Patients will be randomized by the Research Coordinator, ensuring allocation concealment from study investigators. The Research Coordinator will then deliver the randomization number to the inpatient pharmacy, where the medication will be prepared and dispensed by a trained Research Pharmacist. The Research Pharmacist will possess a linkage key to determine which study arm the patient is randomized to, based on the randomization number provided by the Research Coordinator. The assigned treatments will be crosschecked against the master linkage key at the end of the study.

#### Implementation

Patients will be randomized following identification, assessment of study eligibility, and acquisition of patient/parental consent. Randomization will take place 2 weeks before surgery, 1 day before their pre-operative anesthesia consultation. The Research Coordinator will provide the Research Pharmacist with the randomization code prior to their pre-operative appointment. The Research Coordinator will pick up the study medication from the pharmacy and meet with the patient. At this time, they will provide them with the necessary medication and study materials. They will explain how to administer the medication and how to complete the stool diary. They will also answer any trial-related questions. Patients randomized to the standard care trial arm will still be required to complete the stool diary. In circumstances where patients are unable to travel to the hospital to pick up the study medication, the Research Pharmacist will ship medications to them, and all education will be conducted virtually.

#### Blinding

The Research Pharmacist and the Research Coordinator will not be blinded to treatment allocation. Due to the nature of MBP, the patient will be aware of which study arm they have been randomized to. Therefore, the patient will not be blinded.

Patient records will mention that they are part of this study and will include the study number, but the actual medications received (i.e., group allocation) will not be mentioned. The surgical team operating on the patient will be blinded to treatment allocation. The Clinical Outcome Assessor, who will conduct the inpatient post-operative assessments and outpatient follow-up assessment, will also be blinded. The statistician analyzing the data will have a de-identified dataset and will be blinded to group allocation to ensure unbiased analysis. For the purposes of blinding the data analyst, data from the stool diary will be withheld until analysis for all other outcomes is completed.

#### Follow-up

Follow-ups will be completed daily by a Clinical Outcome Assessor while patients are admitted in hospital. There will also be one outpatient follow-up appointment in the Pediatric General Surgery outpatient clinic approximately 2 weeks after surgery. This follow-up visit will coincide with the patient’s regularly scheduled follow-up clinic visit. If the patient is unable to attend the appointment or fails to show up, the follow-up will be conducted by telephone. Visits to the emergency department and readmissions to the hospital between surgery and follow-up will also be recorded. A second follow-up will be completed by the Research Coordinator via telephone 30 days post-discharge.

The family will also be instructed to notify the Research Coordinator in the event that there were complications experienced and managed at another institution or by a family doctor or pediatrician.

#### Loss to follow-up

Full study follow-up will be considered complete 30 days post-discharge. A patient may be discontinued from the study at any time if the family, parent, surgeon, or investigators strongly believe it is not in the patient’s best interest to continue participation. Because all study interventions occur pre-operatively and study follow-up does not differ significantly from the standard follow-up protocol at this institution, the study drop-out rate is anticipated to be low.

#### Data collection

Data collection will be completed by a trained Research Coordinator and Clinical Outcome Assessor. The data collection responsibilities of each are outlined below.

#### Research Coordinator

The Research Coordinator will be responsible for data collection beginning on the day of surgery. They will meet parents in the waiting area and will collect patient demographics, diagnosis, and procedure-related information. Compliance to pre-operative bowel preparation will be assessed using the stool diary. This diary will contain spaces to record the medication doses and the times of administration. The character of the stool will be assessed by parents using a Bristol Stool Chart. Parents will be instructed to return the stool diary to the Research Coordinator on the morning of surgery. The recruitment rate (percentage of eligible patients enrolled), rate of post-randomization exclusions, number of protocol deviations, adverse events, and the number of missed follow-up appointments will also be collected by the Research Coordinator. Patients/parents will be asked to contact the Research Coordinator if they suspect a post-operative infection, who will then refer them to the Clinical Outcome Assessor to confirm whether an infection is present. Finally, the Research Coordinator will contact the patient/parents via telephone 30 days post-discharge and will review the patient’s electronic medical record for any emergency visits during that period.

#### Clinical Outcome Assessor

The Clinical Outcome Assessor will be responsible for collecting data on post-operative infectious complications (superficial and deep SSIs). The SSI will be classified based on the Centres for Disease Control and Prevention definitions [18]. The Clinical Outcome Assessor will be a trained healthcare worker (attending surgeon, surgical fellow, or nurse practitioner) with experience in recognizing infectious complications. They will be responsible for daily patient follow-up in the immediate post-operative period while the patient is admitted to the hospital. They will also conduct the assessment during the follow-up clinic visit after hospital discharge. If a post-operative complication occurs, the mode of treatment will be recorded. If a bacterial culture was obtained, the organism cultured, antibiotics therapy, and duration of antibiotics will be recorded.

#### Statistical analysis

Demographics will be reported as counts with percentages for categorical variables and means with standard deviations for continuous variables. Feasibility outcome measures (e.g., recruitment rate, post-randomization exclusions, protocol deviations, and adverse events) will be reported as proportions. Secondary outcome measures, such as surgical site infections, re-operation, and complications will be reported as proportions. Length of hospital stay and time to full enteric feeds will be reported as means with standard deviation. In cases where continuous data does not follow a normal distribution, medians with interquartile ranges will be used. The SSI risk ratio and risk difference with 95% CIs will be calculated to estimate the minimum clinically important difference based on clinical data. All data will be analyzed with an intention-to-treat approach using IBM SPSS Statistics Version 25.

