**Methods:**

This study aims to determine the feasibility of conducting a randomized controlled trial assessing the efficacy of oral antibiotics, with or without mechanical bowel preparation, in reducing the rates of post-operative infection in pediatric colorectal surgery. Participants aged 3 months to 18 years undergoing elective colorectal surgery will be randomized pre-operatively to one of three trial arms: (1) oral antibiotics; (2) oral antibiotics and mechanical bowel preparation; or (3) standard care. Twelve patients will be included in each trial arm. Feasibility outcomes of interest include the rate of participant recruitment, post-randomization exclusions, protocol deviations, adverse events, and missed follow-up appointments. Secondary outcomes include the rate of post-operative surgical site infections, length of hospital stay, time to full enteral feeds, reoperation, readmission, and complications.

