## Background

Colorectal surgery is associated with high rates of surgical site infections (SSI) in both adult and pediatric populations, occurring in up to 25% of all cases [1]. The American College of Surgeons (ACS) National Surgical Quality Improvement Program (NSQIP) pediatric data shows that colorectal procedures account for 2.5% of all pediatric surgical cases but contribute to 7.1% of the SSI burden [2]. Many of the Canadian centers that currently participate in the NSQIP pediatric program, including our hospital, have higher than expected rates of SSIs in elective colorectal cases. This serves as a great impetus to find the optimal SSI reduction strategy for these patients.

Two pre-operative techniques have been proposed as potential methods of reducing infection in colorectal surgery, oral antibiotics (OA) and mechanical bowel preparation (MBP), which aims to cleanse the large bowel of its fecal contents. The evidence is weak for either of these techniques in the pediatric population, and practice patterns remain variable and largely dependent on surgeon preference. A survey conducted by the American Pediatric Surgical Association (APSA) in 2015 showed that the most common approach taken among pediatric surgeons for all intestinal procedures was MBP alone (31.1%), followed by dietary modifications (26.8%), and OA combined with MBP (19.6%) [2]. The current approach at McMaster Children’s Hospital in pediatric patients undergoing a colorectal procedure is intravenous antibiotics with good coverage against gut flora given on induction of anesthesia, without any bowel preparation.

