**Fig. 1 Fig1:**
[figure not shown]
Trial design

The primary objective of this trial is to determine the feasibility of conducting a RCT to assess the efficacy of OA, with or without the use of MBP, in reducing the rate of post-operative infections in pediatric patients undergoing elective colorectal surgery and to validate key assumptions for a large-scale superiority trial.

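### The observed SSI risk ratio and risk difference cannot estimate a minimum clinically important difference, and with 12 per arm they are too imprecise to serve as a planning effect

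*Protocol article*

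**What the plan says.** Under Statistical analysis, SSI is reported as a proportion, and then: "The SSI risk ratio and risk difference with 95% CIs will be calculated to estimate the minimum clinically important difference based on clinical data". That is the only purpose given for the RR and RD. The article names no other route to an MCID, such as consensus, elicitation from families or clinicians, or a value fixed in advance.

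On size, the Abstract says "Twelve patients will be included in each trial arm", and allocation is 1:1:1, so 36 in total. The Sample size section says "a formal sample size calculation was not conducted" and gives the reason for the number: to "estimate parameters like recruitment rate, treatment adherence, and variability of outcomes, a sample size of 12 per group was selected". A treatment effect is not among the parameters named. SSI is a secondary outcome.

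On what follows, the primary objective is feasibility, and it adds the aim "to validate key assumptions for a large-scale superiority trial". The Abstract and the closing Discussion foresee a fully powered multicentre trial.

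**The concern.** Two separate faults meet in one sentence.

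The first is conceptual. RR and RD describe how far the arms differed in the patients studied. An MCID says how large a difference would have to be for families and surgeons to accept the burden of the preparation. More patients would make the first more precise without turning it into the second. If oral antibiotics truly did nothing, a very large pilot would estimate an RD near zero, and nobody would call zero the smallest difference worth having.

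The second is precision. Even if the sentence is read loosely, as a plan to obtain an effect size for later design, 12 per arm was chosen for other parameters and gives an RD with a very wide interval.

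At stake is what the pilot may claim. A target difference taken from these data would follow the chance position of a few infections, and a trial designed around it could be much too small or needlessly large.

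**Working it through.** **Nothing to reproduce.** The article gives no alpha, power or effect behind "a sample size of 12 per group was selected". The only arithmetic is 3 × 12 = 36.

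**Inputs**
- n = 12 per arm, one pairwise comparison of an active arm with standard care (article).
- True SSI rates are assumptions, shown as a range:
  - 25% vs 14%. The Background puts SSI at "occurring in up to 25% of all cases". Its review of antimicrobial prophylaxis, cited as adult evidence, gives RR 0.56, and 0.25 × 0.56 = 0.14.
  - 20% vs 10%, a middle case.
  - 10% vs 5.6%. The Background's paediatric meta-analysis gives 9.1% without mechanical preparation, rounded to 10%, and 0.10 × 0.56 = 0.056.
- Two-sided 5% and 80% power for the later trial are assumed.

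**Step 1: spread of the observed RD.** SE = √[p₁(1−p₁)/12 + p₂(1−p₂)/12]. At 20% vs 10%: √[(0.16 + 0.09)/12] = 0.144, so a 95% interval is about ±28 points around a true difference of 10. At 25% vs 14%: 0.160, or ±31 points around 11.

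**Step 2: exact binomial enumeration** over all 13 × 13 outcomes:

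| True rates | RD zero or reversed | RD at least twice the truth | At least one of the two arms with no SSI |
|---|---|---|---|
| 25% vs 14% | 33% | 27% | 19% |
| 20% vs 10% | 34% | 22% | 33% |
| 10% vs 5.6% | 51% | 21% | 64% |

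The last column is 1 − [1 − (1−p₁)¹²][1 − (1−p₂)¹²]. At 20% vs 10%: 0.8¹² = 0.069 and 0.9¹² = 0.282, so 1 − 0.931 × 0.718 = 0.33. Within that 33%, the RR (active over standard care) is undefined only when standard care has no events (7%). In the other 26% only the active arm has none, so the RR is 0 and its usual log-scale interval fails.

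**Step 3: one plausible result.** With 3/12 on standard care and 1/12 on active treatment, the reduction is 16.7 points (Newcombe 95% CI −15 to 46). RR = 0.33. SE of log RR = √(1/1 − 1/12 + 1/3 − 1/12) = 1.08, which gives 0.04 to 2.77.

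**Step 4: what if the observed RD became the target?** n per arm = (1.96 + 0.842)² × [p₁(1−p₁) + p₂(1−p₂)] / (p₁−p₂)², with (1.96 + 0.842)² = 7.85.
- 3 vs 2 events (25% vs 16.7%): 7.85 × 0.3264 / 0.00694 ≈ 369
- 3 vs 1 (25% vs 8.3%): 7.85 × 0.2639 / 0.02778 ≈ 75
- 3 vs 0 (25% vs 0%): 7.85 × 0.1875 / 0.0625 ≈ 24
- For comparison, a true 20% vs 10%: 7.85 × 0.25 / 0.01 ≈ 196

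The pooled-variance formula gives 372, 78, 27 and 199, so the choice of formula does not matter. With standard care fixed at 3 events, two infections more or fewer in the active arm move the size about 15-fold. A trial of 75 per arm facing a true 20% vs 10% would have SE = √(0.25/75) = 0.0577 and power Φ(0.10/0.0577 − 1.96) = Φ(−0.23) ≈ 41%.

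**The case against.** The strongest reply is that this is one loosely worded clause about a secondary outcome in a feasibility trial. It sets no rule equating the MCID with the point estimate, and the authors may simply have meant an effect estimate with its interval, to be weighed with other evidence. Reporting RR and RD with 95% CIs is ordinary descriptive practice, and the Sample size section makes no claim that 12 per arm suits a treatment effect.

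Much of this stands, and it limits the point. A reader might infer more than the article supports:
- That the pilot's MCID will set the size of the multicentre trial. The article never says so. The objective speaks of key assumptions without naming an effect size, so mis-sizing is a possible consequence and not a planned one.
- That a chance null or reversed SSI result could stop a worthwhile trial. Table 2 (Progression criteria) has no SSI or efficacy criterion, and the text above it says that no single factor will halt progression.
- That supplying an effect size is the purpose of the pilot. The primary objective and all primary outcomes concern feasibility.
- That the RR would be undefined in a third of pilots at 20% vs 10%. The strict figure is about 7%. The 33% is the chance that either arm has no events.

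What the reply does not remove is the sentence itself. It makes the calculated RR and RD the means of estimating the MCID, and the added reference to clinical data does not change that. The looser reading meets the precision problem instead.

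**Conclusion.** The sentence is wrong as written and should be changed. The conceptual fault needs no assumption: an observed effect is not an MCID at any sample size. The precision fault rests on assumed true rates, but it holds across the range. In a third to a half of such pilots the observed RD would be zero or reversed, which could not serve as a target difference at all. The sample-size illustration depends further on the assumed 80% power and two-sided 5%, and on a step that the article does not describe, so it shows what could happen and not what will.

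Severity is should-fix. The pilot's conduct, its primary outcomes, its 12 per arm and its progression criteria are unaffected. What changes is what the pilot may conclude about SSI.

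**What to change.** In the Statistical analysis section, delete the clause that gives estimating the MCID as the purpose of the RR and RD. Replace it with a statement such as: *SSI counts per arm, and the RR and RD with 95% CIs, are descriptive; they will not define the MCID or the target effect of the main trial.* Say that the MCID will be set separately, from clinical and family judgement and external evidence.

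The pilot may still inform the SSI event rate, reported with its confidence interval. Whether to use only the rate pooled across arms is optional.

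The cost is a sentence or two of wording, with no change to data collection or conduct. The downside is that the pilot no longer claims to supply an MCID.

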#### Data management

All data for this study will be entered into REDCap, a secure, online database designed specifically for the purposes of this trial. All data will be de-identified by substituting patient-specific identifiers with a coded study identification number, such as S102, to ensure anonymity and protect privacy. Any study files containing patient identifiers, including the master list linking participant medical record number to their study identification number, will be stored in password-protected Excel files on the secure drive for the Department of Surgery at McMaster University. This drive is protected by the McMaster University Firewall, and only research staff directly involved in the conduct of this trial will have access to these documents. Paper study forms, including signed consent forms, will be kept in a locked filing cabinet in the secure office space for the Department of Surgery. Only research staff directly involved in the conduct of this trial will have access to this cabinet.

Data checks will be completed throughout the trial to ensure the accuracy of all data entered into the REDCap database. These checks will be completed after subjects 4, 12, and 20, with additional checks done at random throughout the study. All study data will be kept for 15 years in compliance with Health Canada requirements and then destroyed.

#### Data monitoring

This study will be conducted at McMaster Children’s Hospital in partnership with the McMaster Pediatric Surgery Research Collaborative (MPSRC). The Principal Investigator and Research Coordinator will oversee the recruitment of patients, training of research personnel, data collection, and adherence to protocol. They will liaise with all study team members including physicians, residents, and the nurse practitioner to ensure protocol compliance.

This study will also employ a Steering Committee. The Steering Committee members will be responsible for reviewing all protocol deviations, recruitment challenges, and any other significant issues that arise. The Steering Committee will meet every 3 months and will include representatives from Pediatric General Surgery, Infectious Disease, and Biostatistics.

#### Data Safety Monitoring Board

This study will utilize a Data Safety and Monitoring Board (DSMB). The DSMB will be a collaboration of three expert healthcare professionals independent of the Steering Committee and Study Investigational Team who will monitor patient safety during the conduct of the trial. Their role is to review all adverse event (AE) and serious adverse event (SAE) reports from the trial and submit a summary to the Steering Committee and Research Ethics Board. Based on these reports, the DSMB may recommend that the trial be discontinued for safety concerns; however, DSMB members cannot stop the trial for benefit. The DSMB will meet after the first five participants have completed their 30-day post-operative observation. The DSMB will then meet every 6 months thereafter. As needed, the DSMB will convene within 15 days following the notification of any potentially study-related SAE that is non-life-threatening or non-fatal. Additionally, the DSMB will convene within 48 h upon receiving reports of any potentially study-related life-threatening or fatal SAEs. This may be conducted via email or teleconference. To limit bias, DSMB members will be blinded to participant study group allocation.

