#### Interventions

Patients will be randomized to receive either OA + MBP, OA alone, or no preparation (standard of care). If the patient/parents choose not to participate in the trial, the preparation regimen will be at the discretion of the treating surgeon. The trial interventions are detailed in Table 1.

**Table 1 Tab1:** Trial interventions

**Standard care** (all groups)	**Oral antibiotics**	**Mechanical bowel preparation**
• Care according to institutional SSI reduction bundle	Oral non-absorbable antibiotics • Neomycin (15 mg/kg/dose, max of 1 g) To be given the day before surgery at 3 pm, 6 pm, and 9 pm	Two days before surgery No dietary restrictions
		• < 1 year: 5 mL Sennaquil at 4 pm • 1–5 years: 10 mL Sennaquil at 4 pm • > 6 years: 15 mL Sennaquil at 4 pm
	Oral absorbable antibiotics • Metronidazole (15 mg/kg/dose, max of 500 mg) To be given the day before surgery at 3 pm and 9 pm	The day before surgery Light breakfast then clear fluid diet
		• < 1 year: 5 mL Sennaquil at 4 pm • 1–5 years: ¼ sachet Pico-Salax at noon and 4 pm • 6–12 years: ½ sachet Pico-Salax at noon and 4 pm • > 12 years: 1 sachet of Pico-Salax at noon and 4 pm
		The day of surgery
		Care according to standard of care protocol

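### The DSMB has a safety-only mandate but is blinded to allocation with no stated exception, so it is not assured a child's exposure or a by-arm comparison

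*Protocol article*

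**What the plan says.** All of the board's terms are in the protocol article, section Data Safety Monitoring Board.

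- **Task:** "Their role is to review all adverse event (AE) and serious adverse event (SAE) reports from the trial". It then sends a summary to the Steering Committee and the Research Ethics Board.
- **Powers:** "the DSMB may recommend that the trial be discontinued for safety concerns; however, DSMB members cannot stop the trial for benefit".
- **Urgent meetings:** "the DSMB will convene within 15 days following the notification of any potentially study-related SAE that is non-life-threatening or non-fatal", and "the DSMB will convene within 48 h upon receiving reports of any potentially study-related life-threatening or fatal SAEs".
- **Blinding:** "To limit bias, DSMB members will be blinded to participant study group allocation".

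The Interventions section sets three arms: oral antibiotics (OA) with mechanical bowel preparation (MBP), OA alone, and no preparation. The abstract gives 12 children per arm.

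Under Blinding, the patient record omits which study medications were received. The Research Pharmacist and Research Coordinator are unblinded. Under Concealment mechanism, "The Research Pharmacist will possess a linkage key to determine which study arm the patient is randomized to". The Research coordinator section gives that role the collection of adverse events. Nowhere does the article say that either role passes allocation to the board, whether by arm or for a single child.

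**The concern.** The board's task turns on exposure. It must respond to SAEs that may be study-related, and a third of the children are assigned no study preparation. Receipt of a drug does not separate the arms, because every child has antibiotics at induction under the standard-of-care bundle. Nor will a report drawn from the chart reveal the arm, since the chart is kept silent on it.

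The article's own Background makes arm-specific harm a live question. It cites a potential increase in post-operative complications with MBP alone, a pediatric study with more wound infection under MBP than with no preparation (14% against 6%), and another whose findings suggest that adding OA may do harm. Local practice is no bowel preparation. The safety question is therefore between arms, and the safety board is not assured that comparison.

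The primary outcomes include adverse events related to MBP and OA, and Table 2 sets a progression criterion on intervention-related severe events. Relatedness therefore also feeds a feasibility decision.

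**Working it through.** The plan states no figure that depends on this point, so there is none to reproduce. The check is a reading of the text, with simple counts to show scale.

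**Inputs.** Three arms of 12 (Abstract), so 36 children, of whom 24 are assigned a study preparation and 12 are not. Table 2 aims for at most one intervention-related severe event per 30 participants.

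**One SAE.** If nothing else is known about the child and risk is equal in the arms, the chance that no preparation was assigned is 12/36 = 33.3%.

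**Several SAEs, one per child.** The pooled proportion is k/36. If all fall in one arm, that arm's proportion is k/12. With no arm effect, the chance that all k fall in the same arm (any arm) is 3 × C(12,k)/C(36,k).

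| k | Pooled, k/36 | All in one arm, k/12 | Chance with no arm effect |
|---|---|---|---|
| 2 | 5.6% | 16.7% | 31.4% |
| 3 | 8.3% | 25.0% | 3 × 220/7,140 = 9.2% |
| 4 | 11.1% | 33.3% | 3 × 495/58,905 = 2.5% |

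The pooled column is the same however the events are split.

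**A less extreme split.** With four SAEs and no arm effect, the chance that at least three share an arm is 3 × (C(12,3) × 24 + C(12,4))/C(36,4) = 3 × (5,280 + 495)/58,905 = 17,325/58,905 = 29%. By-arm counts could not separate that pattern from chance.

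**Progression criterion.** One per 30 corresponds to 36/30 = 1.2 events over all participants, or 24/30 = 0.8 over those assigned a preparation. A single relatedness judgement can therefore settle it.

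**The stated reason.** The same section makes the board independent of the Steering Committee and the investigational team, and bars it from stopping for benefit. Inpatient and clinic outcome assessment belongs to the Clinical Outcome Assessor. Surgeons, assessor and statistician each have their own blinding. The board's knowing the allocation would not by itself bias any outcome.

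**The case against.** **Blinded need not mean pooled.** A reader might infer that the board sees only pooled counts. The article does not say so; it is silent on report format. Under Blinding, the statistician too is blinded to allocation, yet under Statistical analysis the SSI risk ratio and risk difference must be calculated, which needs data grouped by masked arm. Coded tables are therefore compatible with the sentence. This stands, and the claim is limited to what the text assures the board.

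**A fuller document may cover it.** Report format and case-level unblinding are often set out in a full protocol or board charter, neither of which is shown. That is fair as to silence. But the blinding rule is stated outright with no exception, so it is not mere silence.

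**Others can see.** A reader might infer that nobody sees events and allocation together, or that relatedness cannot be judged at all. The unblinded Research Coordinator collects adverse events, some screening for relatedness precedes the urgent meetings, and timing or event type may hint at exposure. This stands. However, the coordinator is given no between-arm safety review, and the article does not say what information that screening uses.

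**Thirty-six children are too few.** A reader might infer that by-arm tables would reveal a harmful arm statistically. The 29% figure shows that they often would not. This stands.

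**Leakage.** The board's summary goes to a Steering Committee that includes Pediatric General Surgery, and the blinded assessor may be an attending surgeon. This is a real route for arm-level knowledge to reach blinded roles, and the fix must close it.

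**Conclusion.** The concern holds in limited form. The article blinds a safety-only board to allocation with no stated exception, while requiring it to act on possibly study-related SAEs in a trial where a third of children are assigned no study preparation. As written, the board is not given a child's exposure and is not assured a by-arm comparison. The bias rationale has little force for this board.

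The documents do not support saying that the board can see only pooled data, that no role sees both events and allocation, or that a harmful arm would otherwise be detected statistically. The gain lies in judging individual SAEs and noticing clear clustering. No estimate, power or sample size figure changes. The conclusion assumes that no unseen document already provides coded reports or unblinding on request. The counts in the working assume one SAE per child, and the chance figures assume no arm effect. This is a worthwhile, low-cost improvement to safety oversight.

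**What to change.** Amend the blinding sentence in the Data Safety Monitoring Board section along these lines:

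*The DSMB will receive closed tabulations of AEs and SAEs by coded arm (A, B, C), with the number randomised to each as denominator. On request it may obtain the code, or the allocation of an individual child with an SAE.*

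Two further points should be specified:

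- **Data flow.** The tables are built from the Research Coordinator's adverse event data and the Research Pharmacist's key. Both roles are already unblinded, so no new person learns the allocation in preparing them.
- **Containment.** The board's summary to the Steering Committee carries no arm-level information, so that surgeons, outcome assessors and the statistician stay blinded.

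The cost is a wording change, a small added data flow between two existing roles, and a short table for each meeting. The downside is some risk that board members infer which coded arm is which. No clinical rule or stopping criterion changes.
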